### Study setting

The study is set in Dadu District in Sindh Province. The economy in Dadu district is largely agrarian; dependent on crop production, livestock keeping, and agriculture labour. The majority of the population is highly vulnerable to shocks, especially the poorest households, and there are a lack of alternative income sources which are further constrained by lack of opportunities and capital.

About 68 % of the population is classified as poor and very poor households (ACF Household Economy Approach Analysis Report 2013 (HEA)) who have limited access to land. A high proportion of very poor households (87 %) are dependent on incomes from casual labour or self-employment; 90 % of these households are reliant on the markets for food purchase all year long. As a consequence of highly insecure cash incomes and a high reliance on food purchased from markets rather than self-produced, very poor households do not typically meet the average daily recommended caloric intake, consuming 1911 kcal/day instead of 2100 kcal/day. Further, a cross-sectional anthropometric nutrition survey carried out by ACF in Dadu in November 2014, showed that the prevalence of global acute malnutrition (GAM) was approximately 14.3 % (95 % CI 10.8–18.7 %) in children 6–59 months. This is expected to be higher during the summer lean season (June to August), where Dadu also frequently experiences localised flooding and droughts, and high temperatures (above 45 °C). Higher levels of GAM for children from poorer households are also expected.

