### Data collection and management

Three Field Officers are supervising 24 teams, each made up of 1 female and 1 male enumerator. Research Mobilisers are available to help the teams in identifying households and sensitisation about the study.

Quantitative data is collected using ODK software which is a freely available application to design surveys for data collection through smart devices and run on android based platforms. The data are exported into password protected MS Excel on a daily basis and sent to the principal investigator. During the study, children identified with WHZ < −2 (using MOYO charts) [21], MUAC <125 mm and/or oedema are referred to the ACF outpatient treatment programme, whilst remaining in the REFANI-P study. Children with a haemoglobin level < 11.0 g/dl, non-pregnant women <12 g/dl and pregnant women <13 g/dl) are referred for Government of Pakistan nearest health facility for standard treatment.

Qualitative data are being collected by a team of three led by a local lead researcher. Interviews are being recorded then transcribed and translated into English within a week of data collection. The focus group discussions relevant to the cost-effective analysis (CEA) are recorded, transcribed and translated into English. The interviews are also recorded and transcribed and translated if deemed necessary during the course of data collection. Relevant data from the impact study are extracted from the quantitative data set in ODK as described above.

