### Planned statistical analysis

The study will use both quantitative and qualitative data analytical methods and a cost-effectiveness analysis will be done. The key steps for the quantitative data analysis of outcome measurements will be: 1) cluster level analyses using summary measures between the different time points and 2) individual level analyses adjusted for clustering (longitudinal generalised mixed models). Significance will be assessed at *p* < 0.05 level.

Baseline descriptive analyses will be carried out on all independent variables at cluster and individual levels to assess baseline differences between groups. The data will be examined for outliers, normality and missing data. To test the overall effect of the interventions (on an intention-to-treat basis), changes in outcome variables between the different groups over follow-up measurements (6 months and at 1 year) will be compared. The interventions, measurement time and intervention-time interaction will be included as fixed effects in the models. Children, mothers and villages will be included as random effects in the intercept and in the slope of the different repeated measurements. Potential confounders (e.g. sex, age and baseline nutrition status) will be used if there are differences at baseline. Best fit of the data will be assessed using maximum likelihood ratio tests.

We will examine the data to determine the extent and type of differential attrition, and depending on our findings, we may apply an appropriate adjustment to estimates of intervention effect and/or discuss the possible consequences they may have on the reliability of the estimates. Since there will be more than one child per household in many cases, a secondary analysis using one child per household (selected at random) will be carried out to confirm if results are being driven by a smaller number of larger households. A mediation analysis (using seeming unrelated regression methods [22–24]) will be carried out to measure the extent to which increased mediating variables may mediate the relationship between the different interventions and comparison group and wasting. All quantitative analyses will be carried out in Stata 13.1. Z-scores will be generated using the World Health Organisation (WHO) macro for Stata.

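### The mixed model gives villages only a random intercept and slope; if time is coded by visit, the test of change to month 6 can reject too often

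*Protocol article*

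**What the plan says.** All of the analysis text is in the protocol article, Planned statistical analysis.

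- Two steps are listed: "1) cluster level analyses using summary measures between the different time points and 2) individual level analyses adjusted for clustering (longitudinal generalised mixed models"). Neither is named as the one that decides. The criterion is "Significance will be assessed at *p* < 0.05 level".
- Fixed part of the model: "The interventions, measurement time and intervention-time interaction will be included as fixed effects in the models". Whether time is a category per visit or a linear term is not stated.
- Random part: "Children, mothers and villages will be included as random effects in the intercept and in the slope of the different repeated measurements".
- Target of the comparison: "changes in outcome variables between the different groups over follow-up measurements (6 months and at 1 year) will be compared".
- Model checking: "Best fit of the data will be assessed using maximum likelihood ratio tests".

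Outcome measures sets eight rounds (months 0 to 6, and 12). Randomisation makes the village the randomised unit. Study setting describes the summer lean season as a time "where Dadu also frequently experiences localised flooding and droughts".

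**The concern.** Arms are compared on change between rounds, and villages were randomised. The standard error must therefore reflect how much the mean change differs from village to village for reasons other than treatment. A village intercept cancels out of a change. One straight-line slope fitted over several rounds captures villages that drift steadily. It captures only part of a deviation that appears in one round and then goes, such as a flood that affects a few villages in one month. The rest is left to the child-level terms, where it is averaged over about 45 children and looks much smaller than it is.

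At stake are the confidence intervals and p-values of the month-6 comparisons with the control arm for mean WHZ, one of the two primary outcomes. Any error is in the direction of false positives.

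**Working it through.** **Inputs from Sample size.** ICC 0.02; average cluster size 50; dropout 10%; coefficient of variation of cluster size 0.65; WHZ SD 1.10; 2.2 eligible children per household; 632 households per group. Children per village after dropout: 50 × 0.9 = 45. Villages per arm are not stated: 632 × 2.2 / 50 = 27.8, about 28, if 50 counts children; 632 / 50 = 12.6, about 13, if it counts households.

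**The plan's own figure.** For a 0.19 WHZ difference at two-sided 5% and 80% power, 2 × (1.96 + 0.84)² × 1.10² / 0.19² gives 527 children per arm after rounding up. The design effect is 1 + ((1 + 0.65²) × 50 − 1) × 0.02 = 2.4025. Then 527 × 2.4025 / 0.9 / 2.2 = 639 households, 1.2% from the stated 632. The inputs are therefore read as intended, and the sample size itself is not affected by this point.

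**Assumptions not in the article.** Village round-to-round correlation ρ from 0.6 to 1.0; within-child WHZ correlation r of about 0.55 to 0.71; time coded by visit; balanced clusters; total variance scaled to 1.

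**Simple bound.** The variance of a village's mean change from month 0 to 6 has two parts:

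- village part: 2 × 0.02 × (1 − ρ)
- child part: 2 × 0.98 × (1 − r) / 45, which is 0.0196 at r = 0.55 and 0.0131 at r = 0.70

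If the model missed the whole village part, its standard error would be too small by the factor √(child / (child + village)), and the true error of a nominal 5% test would be 2Φ(−1.96 × factor).

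| ρ | Village part | Factor, r = 0.55 | Error | Factor, r = 0.70 | Error |
|---|---|---|---|---|---|
| 1.0 | 0 | 1.000 | 5.0% | 1.000 | 5.0% |
| 0.9 | 0.004 | 0.911 | 7.4% | 0.875 | 8.6% |
| 0.8 | 0.008 | 0.843 | 9.9% | 0.788 | 12.3% |
| 0.6 | 0.016 | 0.742 | 14.6% | 0.670 | 18.9% |

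This is the case with a village intercept alone. The planned slope absorbs part of the village variation, so the planned model does better.

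**The planned model.** The village intercept-and-slope model was fitted by maximum likelihood to the expected covariance, and its variance for the month-0-to-6 change was compared with the true one.

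| ρ | 8 rounds, r = 0.55 | 8 rounds, r = 0.71 | Rounds 0, 6, 12, r = 0.55 | Rounds 0, 6, 12, r = 0.71 |
|---|---|---|---|---|
| 0.9 | 6.8% | 7.8% | 6.6% | 7.5% |
| 0.8 | 8.5% | 10.3% | 8.1% | 9.6% |
| 0.6 | 11.6% | 14.4% | 10.8% | 13.1% |

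At ρ = 1.0 the error is 5.0%. With the slope kept, the month-12 contrast is at 5-7%.

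**Simulation** (clusters of 50, r = 0.7, 28 villages per arm, 1,500 runs per setting). With eight rounds the mixed-model test rejected 5.5%, 7.7% and 9.7% of the time at ρ = 1.0, 0.9 and 0.8. With three rounds it rejected 4.9%, 7.9% and 9.5%. With 13 villages per arm it rejected 7.4-8.6% at 0.9 and 10.4-10.7% at 0.8. A t-test on village mean change stayed at 4.0-6.7% across all settings, which also included ρ = 0.5. In a separate simulation, adding a village-by-round variance to the model gave 4.7-6.4%.

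**Where the problem does not arise.** With linear time in the fixed part and the village slope kept, the arm-by-slope test is at 5.0% for every ρ tried. With only two rounds in a model, an intercept and a slope leave the variance of village change free, so nothing is missed.

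**The case against.** The strongest reply is that the article already plans a cluster-level analysis of change, listed before the mixed model, and that analysis has the right error term. This stands. It protects the conclusion only if that analysis decides, which the article does not say; both steps are judged at the same 5% level.

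The second reply is that the inflation needs a particular combination: time by visit in the fixed part with a linear village slope over three or more rounds. This also stands. The phrase about the slope of the different repeated measurements could even mean one coefficient per round, which would come close to the remedy below. The combination is still a natural reading, since separate comparisons at 6 months and 1 year do not follow from one linear term over 12 months.

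The third is that an article without its analysis plan may leave covariance details out. But the article does state the random effects, so the wording can be judged as it stands.

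Several stronger readings are tempting and not supported:

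- *That the month-6 test does reject too often.* The round-to-round village correlation is not given, and at 1.0 there is no inflation. Flooding and drought are named as features of the setting, with no effect on WHZ quantified.
- *That enumerator teams add to the problem.* The article says "Three Field Officers are supervising 24 teams, each made up of 1 female and 1 male enumerator" but not that teams rotate. A team that stays with its villages has a persistent effect, which the intercept absorbs.
- *That every local shock is treated as independent child noise.* The village intercept and slope absorb part of it. A test of the month-6 level rather than the change is only mildly inflated, at 5.5-8.1% with clusters of 50 and eight rounds.
- *That likelihood ratio tests will remove the village slope.* If they did, the month-6 error would be about 7-9%, 10-12% and 14-18% at correlations of 0.9, 0.8 and 0.6. The article says only that fit will be assessed, not that terms will be dropped.

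**Conclusion.** The point holds conditionally. With time coded by visit and village effects that are not perfectly correlated between rounds, the random effects as written can make the mixed-model test of the month-6 change too liberal: about 7-8%, 8-10% and 11-14% at correlations of 0.9, 0.8 and 0.6, instead of 5%. These figures rest on mean WHZ, ICC 0.02, about 45 children per village, balanced clusters and the assumed correlations. The stated variation in cluster size was not built in, and the wasting model was not checked, so no size is claimed for that outcome. The finding is an unprotected month-6 comparison in one of two planned analyses. It does not show that the trial's error rate fails.

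**What to change.** Any one of these would do:

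1. In each longitudinal model add a village-by-round random intercept beside the village intercept (in Stata, a village-level R.round term with identity covariance), and keep it whatever a likelihood ratio test shows.
2. Report the fixed effects with standard errors clustered on village. This is reliable with about 4 × 28 = 112 villages; with about 4 × 13 = 52, add a small-sample correction.
3. Name the planned cluster-level analysis of change as the deciding test, with the mixed model as supporting.

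Whichever is chosen, state whether time is by visit or linear in the fixed and in the random part. The cost is a sentence of analysis text and, for the first two, about one line of code. The downside is somewhat wider intervals at month 6; if the extra village variance proves to be near zero, almost nothing is lost.

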### Sample size

To determine the minimum detectable difference in prevalence of wasting for this sample size the following information was used: 1) estimated prevalence of wasting at baseline (16 %); 2) an estimate of the intra-class correlation coefficient (ICC) from a previous survey (0.02); 3) an estimate of the average cluster size (50); 4) for unequal cluster sizes an estimate of the coefficient of variation of cluster sizes (0.65); 5) significance level at 5 % and power of at least 80 %; 6) a likely dropout rate of 10 %; and 7) the estimated number of eligible children per household (2.2).

The sample size is 632 households per intervention group. This sample size is sufficient to measure a detectable difference of 7 % between the intervention groups and the comparison group post intervention. The sample is powered to detect a 0.19 WHZ difference between the intervention and comparison groups (based on a baseline mean of −1.22 (1.10), from previous data).

Sample size calculations were carried out in Stata (SE version 13.1; StataCorp, Special Edition, College Station, Texas 77845 USA) using the [*clustersampsi*] command.

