### Randomisation

The unit of randomisation is villages stratified by village size (blocks of small, medium and large) to achieve similar numbers of children in each intervention group of the study and ensure an equal distribution of variables at baseline. Due to the likelihood of tensions between villages being created through a public randomisation process, randomisation is done separately by the principal investigator (PI) putting village names into a bowl and drawing out one at a time to add to an ‘intervention’ bowl.

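### Sex, age and baseline nutrition status enter the models only if they happen to differ at baseline, by no stated criterion, so chance imbalance picks the primary model and precision is given up when nothing is flagged

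*Protocol article*

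**What the plan says.** All of this is in the protocol article.

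- **Covariates** (Planned statistical analysis): "Potential confounders (e.g. sex, age and baseline nutrition status) will be used if there are differences at baseline". The list is open-ended. No size of difference, test or threshold is given, and with four arms no contrast is named as the trigger.
- **How differences are found** (same section): "Baseline descriptive analyses will be carried out on all independent variables at cluster and individual levels to assess baseline differences between groups".
- **Model terms** (same section): "The interventions, measurement time and intervention-time interaction will be included as fixed effects in the models", and "Children, mothers and villages will be included as random effects in the intercept and in the slope of the different repeated measurements". Village size is in neither list.
- **What is compared** (same section): "changes in outcome variables between the different groups over follow-up measurements (6 months and at 1 year) will be compared", by intention to treat.
- **Randomisation**: "The unit of randomisation is villages stratified by village size (blocks of small, medium and large").
- **Sample size**: "significance level at 5 % and power of at least 80" %, with no allowance for baseline adjustment.

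Table 2 shows that the child's age, sex, weight and height are all recorded at baseline, and that weight and height are recorded at every later visit.

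**The concern.** In a randomised trial a covariate earns its place by predicting the outcome, not by looking unbalanced. A conditional rule has three costs.

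1. The primary model is not known until the data have been inspected. Because no criterion is given, two analysts could reach different models from the same data.
2. When no difference is flagged, the model forgoes the precision that baseline WHZ, age and sex could supply.
3. An imbalance just too small to be flagged stays in the estimate. A comparison of changes does not remove it. It over-corrects, by (1 − r) times the imbalance, where r is the baseline-to-follow-up correlation.

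A separate and smaller matter is that villages are randomised within size classes, while the listed terms do not carry that stratum into the analysis.

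**Working it through.** **Inputs from the Sample size section.** WHZ SD 1.10; target difference 0.19; ICC 0.02; mean cluster size 50; coefficient of variation of cluster size 0.65; dropout 10%; 2.2 eligible children per household; 632 households per group; 5% significance (two-sided assumed); 80% power.

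**Assumed, because the article does not give them.** Correlation r between baseline and follow-up WHZ: 0.6, range 0.5–0.7. Where a trigger is needed, a difference is taken to mean p < 0.05.

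**Step 1: reproduce the plan's figure.**
- Individually randomised n per arm: 2 × (1.96 + 0.84)² × 1.10² / 0.19², giving 527.
- Design effect: 1 + ((1 + 0.65²) × 50 − 1) × 0.02 = 2.4025.
- Households: 527 × 2.4025 / 0.9 / 2.2 = 639, or 633 if dropout is applied as × 1.1. The plan has 632, so the figure reproduces with no baseline adjustment.
- Effective n after dropout: 632 × 2.2 × 0.9 / 2.4025 = 521 per arm. The detectable difference is 0.191, and power for 0.19 is 79.6%.

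**Step 2: adjusting for baseline against comparing changes.** Relative to the follow-up variance, a change has variance 2(1 − r) and a baseline-adjusted comparison 1 − r². Their ratio is (1 + r)/2.

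| r | Change | Adjusted | Ratio | Detectable, change | Detectable, adjusted | Power for 0.19, change | Power for 0.19, adjusted |
|---|---|---|---|---|---|---|---|
| 0.5 | 1.00 | 0.75 | 0.75 | 0.191 | 0.165 | 79.6% | 89.6% |
| 0.6 | 0.80 | 0.64 | 0.80 | 0.171 | 0.153 | 87.6% | 93.6% |
| 0.7 | 0.60 | 0.51 | 0.85 | 0.148 | 0.136 | 94.9% | 97.4% |

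The table starts from 0.191. Starting from the plan's 0.19 at r = 0.6 gives 0.19 × √0.80 = 0.170 and 0.19 × √0.64 = 0.152.

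**Step 3: how far this depends on the village component.** Step 2 assumes that the between-village variance shrinks in the same proportion. The design effect splits into 0.98 at child level (1 − 0.02) and 1.4225 at village level (1.4225 × 50 × 0.02), so 1.4225 / 2.4025 = 59% of arm-mean variance is between villages. If that part does not shrink, at r = 0.6:
- change: 0.19 × √((0.80 × 0.98 + 1.4225) / 2.4025) = 0.182
- adjusted: 0.19 × √((0.64 × 0.98 + 1.4225) / 2.4025) = 0.175

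**Step 4: imbalance left in when nothing is flagged.** At baseline, effective n is 632 × 2.2 / 2.4025 = 579 per arm. The SE of a WHZ difference is 1.10 × √(2/579) = 0.065. Under the assumed trigger, an imbalance of up to about 0.127 goes unadjusted. It would shift a comparison of changes by (1 − 0.6) × 0.127 = 0.05 WHZ, about 27% of 0.19 (33% at r = 0.5, 20% at r = 0.7). This takes the same r for village means as for children.

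**Step 5: error rate of the conditional rule.** A simulation on village means (28 villages per arm, 4,000 runs, one two-arm contrast, no stratum effect) compared adjusting only when baseline p < 0.05 with always adjusting.
- r = 0.5: SE 0.261 against 0.233; type I error of the conditional rule about 4.4%.
- r = 0.7: SE 0.251 against 0.196; type I error about 3.8%.

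The fallback model in this simulation was follow-up-only. At r = 0.5 a change has the same variance and the same size of dependence on baseline, so that row carries over. The r = 0.7 row overstates the effect for a comparison of changes. The direction is the same either way: screening out large imbalances narrows the spread of the estimate, but its standard error does not shrink to match.

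**Step 6: the stratum.** With an assumed shift of 0.5 SD of village means per size class, omitting the stratum from an unadjusted follow-up comparison gave type I error of 3.9% and 3.2% (r = 0.5 and 0.7), against 5.6% and 4.7% with it included. Once baseline was a covariate, adding the stratum hardly changed the SE (0.2396 to 0.2386, and 0.1947 to 0.1944). The simulated shift was the same at baseline and follow-up, so it would also cancel from a comparison of changes.

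**The case against.** The strongest reply is that baseline WHZ is not ignored. The plan describes a longitudinal mixed model with an arm-by-time term and a comparison of changes, and month 0 is probably one of the repeated outcomes. That stands. A reader might infer that the best predictor of follow-up WHZ is simply left out, so that adjustment would save 36% of variance (1 − 0.64) and bring 0.19 down to 0.15. Those figures need a follow-up-only comparison, which the article does not describe, and also a village component that shrinks in proportion. The fair comparator is the change analysis in steps 2 and 3.

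Other parts of the reply also stand:

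- **Significance tests of balance.** The article plans descriptive baseline analyses and states no test. The p < 0.05 trigger used above is an assumption.
- **Stratum.** An article may leave this term to a fuller plan, and the covariate list is open. A claim that the analysis ignores the randomisation scheme goes further than the text. Step 6 also suggests that little precision is at stake once baseline is handled.
- **Wasting.** It is tempting to say that comparing changes in wasting has 40% more variance than follow-up alone at a correlation of 0.3. That applies a linear change-score formula to a binary outcome for which generalised mixed models are planned, so it is not relied on here.

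The conditional sentence itself is not rescued by any of this. It is a stated rule, not a detail left for later.

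**Conclusion.** The point holds for the conditional covariate rule: it has no criterion, and it lets chance differences decide the primary model. Against the planned comparison of changes, the child-level variance forgone is about 20% (15–25% for r of 0.5–0.7). At r = 0.6 that is a detectable WHZ difference of about 0.170 rather than 0.152 under proportional shrinkage, and 0.182 rather than 0.175 if the village component does not shrink. The correlation and the trigger are assumptions.

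A reader might infer that the rule inflates false positives or undermines the sample size. Neither is supported. The simulated error rates lie at or somewhat below 5%, and the 632 households reproduce without any adjustment. The harm is lost power, some residual chance imbalance and a mildly conservative test. The missing stratum is a secondary point. This is worth correcting because the correction is nearly free, not because the trial's main conclusion would otherwise be invalid.

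**What to change.** Replace the conditional sentence with a rule that all primary models include, whatever the observed balance, age, sex, village-size stratum and the baseline value of the outcome. State which of two forms is used for baseline:

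- as a covariate, with month 0 removed from the repeated outcomes; or
- as a repeated outcome at month 0, with baseline means constrained equal across arms.

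Keeping month 0 as an unconstrained outcome and also entering it as a covariate would use the same measurement twice.

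Include the stratum in the cluster-level analysis as well, and keep the baseline comparisons descriptive, with no role in choosing the model.

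The cost is wording and model specification. Child age, sex and anthropometry are already collected at baseline, and village size was needed for the randomisation. Three size classes use two degrees of freedom, with about 28 villages per arm (632 × 2.2 / 50 = 27.8). The article reports recruitment closed and the trial ongoing, so the change should be dated and recorded before outcomes are compared by arm.

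### The large-household check keeps one random child per household, which is valid but noisier than it need be; combining many draws or weighting by inverse household size would answer the same question better

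*Protocol article*

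**What the plan says.** The protocol article includes every eligible child of every eligible household (Study design). The main individual-level model has children, mothers and villages as random effects (Planned statistical analysis). The same section then adds a robustness check: "a secondary analysis using one child per household (selected at random) will be carried out to confirm if results are being driven by" a minority of larger households. It sets p < 0.05 as the general significance level. It does not say whether the check is read by significance or by comparing estimates, or whether the draw is made once or repeatedly.

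The Sample size section gives "the estimated number of eligible children per household (2.2") among its inputs and sizes the trial for the all-children analysis. It claims no power for the one-child check.

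**The concern.** The check asks whether the result would look much the same if each household counted equally. Keeping one child answers that, but with fewer than half the children and a dependence on which sibling happened to be picked. An estimate that moves, or a p-value that crosses 0.05, can then come from lost sample and the luck of the draw. A reader could take either as a sign that a few large households produced the effect. The protocol itself treats that as a possibility worth testing, so the check should be able to tell the two apart as well as the data allow.

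**Working it through.** **Inputs (Sample size section).** 632 households per group; 2.2 eligible children per household; dropout 10%; ICC 0.02; average cluster size 50, read as children; coefficient of variation of cluster size 0.65; "significance level at 5 % and power of at least 80" %, taken as two-sided; WHZ SD 1.10; wasting 16% at baseline. Like the protocol's own figures, these calculations concern a single time point.

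**1. Reproduce the protocol's figure.**
- Design effect = 1 + ((1 + CV²)m − 1) × ICC = 1 + (1.4225 × 50 − 1) × 0.02 = 2.4025.
- For 0.19 WHZ, 527 independent children per group are needed. 527 × 2.4025 / 0.9 / 2.2 = 639 households, against 632 stated.
- Conversely, 632 × 2.2 × 0.9 = 1,251 children. Effective n = 1,251 / 2.4025 = 521. SE = 1.10 × √(2/521) = 0.0682. Detectable difference = 2.80 × 0.0682 = 0.191. Power at 0.19 = 79.6%.

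The stated design is reproduced.

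**2. One child per household.**
- Share dropped: 1 − 1/2.2 = 54.5%.
- Children kept: 632 × 0.9 = 569 per group.
- Cluster size falls with the draw: 50 / 2.2 = 22.7. With the same CV, the design effect is 1 + (1.4225 × 22.7 − 1) × 0.02 = 1.63.
- Effective n = 350. SE = 1.10 × √(2/350) = 0.0832. Detectable difference = 0.233.

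| Comparison | All children | One child |
|---|---|---|
| WHZ, difference 0.19 | 79.6% | 62.7% |
| Wasting, 16% v 9% | 92.8% | 80.1% |
| Wasting, 16% v 23% | 81.5% | 64.7% |

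**3. How often the check loses significance after a significant primary result.** The one-child sample is nested in the full sample, so the two test statistics are correlated at about √(350/521) = 0.82. With a true difference of 0.19 WHZ, both are significant with probability about 0.604. The conditional failure rate is 1 − 0.604/0.796 = 24%. Step 1 treats siblings as no more alike than children of the same village. With an assumed sibling correlation of 0.2 to 0.3, all-children power falls to about 72% to 76% and the conditional failure rate to about 17% to 21%.

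**4. Noise from the choice of sibling.** Relative to using the household mean, the draw adds variance 2 × 1.10² × (1 − ρ) × E[1 − 1/s] / 569 to the group difference, where s is household size and ρ the sibling correlation. The documents give neither ρ nor the spread of s, so both are assumed, with mean size 2.2.
- Sizes 2 and 3 (80%, 20%), ρ = 0.02: E[1 − 1/s] = 0.533; SD = √(2 × 1.21 × 0.98 × 0.533 / 569) = 0.047.
- Sizes 1 to 5 (35%, 30%, 20%, 10%, 5%), ρ = 0.5: E[1 − 1/s] = 0.398; SD = √(2 × 1.21 × 0.5 × 0.398 / 569) = 0.029.

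So the SD is about 0.03 to 0.05 WHZ, or 15% to 25% of the 0.19 target.

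**5. What equal household weight over all children recovers.** This removes the variance in step 4. SE = √(0.0832² − 0.047²) = 0.0686 in the first case and √(0.0832² − 0.029²) = 0.078 in the second. Power at 0.19 WHZ is then about 79% and 68%. On the same assumptions, power for wasting of 16% against 9% is about 85% to 93%.

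**The case against.** The strongest reply is that nothing here is wrong. The draw is unbiased for the household-equal effect, it is labelled secondary, and no power was promised for it. That stands: this is a gain in efficiency and ease of interpretation, not the correction of an error.

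Four stronger readings are tempting, and the documents do not support them.
- A reader might infer that 37% of checks (1 − 62.7%) would fail to confirm a true effect. That rate ignores the nesting. The relevant figure, given a significant primary WHZ result, is about 24% or lower.
- A reader might apply the 63% power to both primary outcomes. It belongs to mean WHZ. For a fall in wasting from 16% to 9%, the direction of benefit, power stays near 80%.
- A reader might infer that a non-significant check will be taken as proof of dominance. The section states a general 5% level but no such rule for this check.
- A reader might infer a single draw. The sentence most naturally reads that way, but it does not exclude repetition, and the number of draws may be set in the full plan.

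It is also fair to object that weighting is not a drop-in change. Child-level weights in the planned multilevel model need choices of level and scaling, and would not automatically give each household equal weight. That objection is met by using a marginal model for this check.

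**Conclusion.** The point holds as a modest, nearly free improvement to a stated method. The check discards 54.5% of children and lowers WHZ power at 0.19 from about 80% to 63%. It would lose significance in roughly a quarter of trials with a significant primary WHZ result, even with no large-household dominance. Comparing estimates instead of p-values does not fully rescue a single draw, because the choice of sibling still moves the estimate by an SD of about 0.03 to 0.05 WHZ. The power figures rest on the protocol's inputs, a two-sided test, a cluster size of 50 children and an unchanged CV after thinning. The 24% rests on a nested-sample approximation. The draw noise and the recovered power also rest on assumed sibling correlations of 0.02 to 0.5 and assumed household-size mixes. The primary analysis is not in question.

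**What to change.** Keep the question and change the estimator, in one of two ways:
- repeat the one-child draw many times and combine the results (multiple outputation), with the number of draws and the seed fixed in advance; or
- fit a marginal model to all children, weighting each by 1/(number of eligible children in the household), with village-clustered standard errors. The weight must be the inverse of household size, and it should not be put into the multilevel model.

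Add a sentence saying that the check is judged by how far the estimate and its confidence interval move from the all-children analysis, not by whether p stays below 0.05.

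The cost is a little more analysis work: one derived weight or a loop over draws, and no new data. The gain is partial, with WHZ power of about 68% to 79% instead of 63%, depending on sibling correlation and household-size spread. Both can be estimated from the baseline data.
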